# Comparing the effect of in-person and virtual childbirth preparation trainings on the fear of childbirth (FOC) and pregnancy experience of pregnant women: protocol for a quasi-experimental feasibility study

**DOI:** 10.1186/s40814-021-00933-w

**Published:** 2021-11-05

**Keywords:** Childbirth preparation, Fear of childbirth, Pregnancy experience, Type of delivery, Virtual education, Feasibility study

## Abstract

**Background:**

Childbirth preparation trainings are an important component of prenatal education, and pregnant women are increasingly interested in seeking information from online sources. The aim of this study is to compare the feasibility and the effects of in-person and virtual childbirth preparation training courses on the pregnancy experience, fear of childbirth (FOC), birth preference, and type of delivery among pregnant women.

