The primary objective of study is the feasibility of recruitment and feasibility of intervention adherence of participants in both in-person and virtual education groups. The secondary objectives are the effect of childbirth preparation training courses using two in-person and virtual education methods on the pregnancy experience, FOC, birth preference, and type of delivery in pregnant women.

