### Measurements and feasibility outcomes

The primary outcome of the present study would be the study feasibility that will be assessed based on recruitment and intervention adherence for all of the participants in both groups.

The secondary outcome of the present study would be the improvement of pregnancy experience measured by the brief version of the pregnancy experience scale (PES) [19]. The secondary outcome would be the decreased FOC measured by the version A of Wijma Delivery expectancy/experience questionnaire (WDEQ-A) [20]. In addition, the other outcomes would be the birth preference and type of delivery, respectively. Data collection is shown in the flow diagram (Fig. 1). Data will be collected at 3 times by self-reporting method through Telegram messages: Recruitment (demographic characteristics questionnaire, PES, WDEQ-A) ≈ 18-20 weeks (T1); 36-38 weeks (PES, WDEQ-A, and birth preference) (T2); the first few days of postpartum (type of delivery) (T3).

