### Analytic plan

Feasibility of recruitment will be achieved if ≥ 30% of eligible participants enroll in the study, and ≥ 80% participants complete follow-up assessments at 36-38 weeks (PES, WDEQ-A, and birth preference) (T2); the first few days of postpartum (type of delivery) (T3). Feasibility of intervention adherence will be achieved if average proportion of intervention adherence rate is ≥ 0.8 (participating in six sessions from eight at least for both the virtual and in-person childbirth preparation training groups).

The collected data will be analyzed in the SPSS software (version 19) using descriptive statistics, such as frequency distribution tables. Also, the Chi-square test and one-way analysis of variance (ANOVA) will be used to compare the quantitative and qualitative variables in three groups, respectively. In addition, the paired *t* test will be employed for intragroup comparison. The *p* value of less than 0.05 will be considered statistically significant.

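### The Abstract aims to compare the feasibility of the two formats, the Introduction's objective does not, and the adherence rule neither compares them nor says whether 0.8 applies per format or pooled

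*Protocol article*

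**What the plan says.** The documents put the feasibility aim in two ways.

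- **Abstract, Background:** comparative. "The aim of this study is to compare the feasibility and the effects of in-person and virtual childbirth preparation training courses".
- **Introduction, closing paragraph:** not comparative. "The primary objective of study is the feasibility of recruitment and feasibility of intervention adherence of participants in both in-person and virtual education groups". The section on measurements and feasibility outcomes agrees: feasibility is to be "assessed based on recruitment and intervention adherence for all of the participants in both groups". The Discussion also speaks of evaluating feasibility, not comparing it.

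The Analytic plan then sets three cut-offs:

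- **Recruitment:** "Feasibility of recruitment will be achieved if ≥ 30% of eligible participants enroll in the study". This is one overall figure.
- **Follow-up:** "≥ 80% participants complete follow-up assessments at 36-38 weeks", together with the postpartum record of delivery type. It is not split by format.
- **Adherence:** "Feasibility of intervention adherence will be achieved if average proportion of intervention adherence rate is ≥ 0.8", with adherence explained as "participating in six sessions from eight at least for both the virtual and in-person childbirth preparation training groups".

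The only between-group methods named are a chi-square test and a one-way ANOVA across the three groups. No feasibility measure is named as an input to either.

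**The concern.** Feasibility is the primary outcome, and a reader of the Abstract will expect the trial to say how the two formats compare on it. The cut-offs cannot do that. They give a yes or no on an observed proportion and take no account of sampling error or of the gap between formats.

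The adherence rule adds an ambiguity of its own. An average proportion may mean one average per format or one average over both. The parenthesis says that the six-of-eight definition holds for both groups, but not that each group must reach 0.8 by itself. The two readings can give opposite verdicts on the same data.

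The Introduction says it is unclear whether virtual delivery will be feasible in Iran, and the Discussion says the results will be used to refine the intervention and seek a larger grant. The adherence of the virtual format, alone and beside the in-person format, is therefore the figure the next study needs.

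**Working it through.** **Inputs.** 55 women per group (Sample size). Adherence cut-off 0.8, with adherence meaning at least six of eight sessions (Analytic plan). I take adherence as the share of women who meet that definition. The plan gives no precision calculation for feasibility, so there is no figure of its own to reproduce. The counts below are illustrations, not figures from the documents.

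**Reading 1: 0.8 required of each format.** The lowest passing count is 0.8 × 55 = 44.

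- 44/55 = 80.0% and 54/55 = 98.2%. Both pass.
- Difference: 10/55 = 18.2 points.
- Wilson 95% intervals: 67.6% to 88.4% for 44/55, and 90.4% to 99.7% for 54/55.
- Newcombe lower limit: 0.182 − √[(0.982 − 0.904)² + (0.884 − 0.800)²] = 0.067.
- Newcombe upper limit: 0.182 + √[(0.997 − 0.982)² + (0.800 − 0.676)²] = 0.306.
- 95% CI: 6.7 to 30.6 points.

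On this reading two passing formats can differ by at most 20 points (80% against 100%).

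**Reading 2: 0.8 required of the pooled average.**

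- (34 + 54)/110 = 88/110 = 0.80, which passes.
- 34/55 = 61.8% and 54/55 = 98.2%. Difference: 20/55 = 36.4 points, Newcombe 95% CI 22 to 50.

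Under reading 1 the same data fail, because 61.8% is below 80%.

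**Precision at the planned size.**

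- Both formats at 44/55: the Newcombe CI for the difference is −15.0 to +15.0 points.
- Both formats near 90%: at 49/55 each the half-width is 12.4 points, and at 50/55 each it is 11.7, so about 12. The simple formula 1.96 × √(2 × 0.9 × 0.1/55) gives 11.2.

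**Behaviour of the point-estimate rule for one format.** With X binomial on 55 women:

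- P(X ≥ 44) at true adherence 0.75 = 0.246, so such a format passes about 25% of the time.
- P(X ≥ 44) at true adherence 0.80 = 0.580, so a format exactly at the cut-off fails about 42% of the time.

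**Denominator.** The inclusion and exclusion section and the Intervention section remove virtual participants who do not respond and in-person participants with low attendance. These are the women whose adherence is in question. As an illustration, 43 adherers among 55 enrolled is 78.2%, a fail. If five non-adherers are excluded first, 43/50 = 86.0%, a pass.

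**The case against.** The strongest reply is that the operative statement is the Introduction's primary objective, which is not comparative. The sections on outcomes and the Discussion support it, and the cut-offs fit it. On that view the Abstract's sentence is loose condensation, with one verb covering both feasibility and effects. This stands to the extent that rewording the Abstract is a full remedy. It does not remove the contradiction, and it does not settle how the 0.8 is averaged.

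Second, the frequency tables and the three-group chi-square could cover follow-up completion, which exists in all three groups. That is fair. They cannot cover adherence, because the control group receives no training and has no sessions to attend.

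Third, fixed progression cut-offs are normal in feasibility work, and an article may leave the choice of interval to a fuller document. That is also fair, and cut-offs as such are not the fault. The point is that the rule the article does state neither serves the Abstract's aim nor has a single reading.

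Fourth, a between-format difference would be hard to interpret. Allocation is not described as random, six of eight sessions is already compulsory for women who wish to deliver at this hospital (Setting), and the two formats have different exclusion rules. This stands as a limit on what the difference can show. A confidence interval reflects sampling error only.

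A reader might go further and infer that the primary objective receives no estimate at all, or that the authors mean to treat two passes as equal feasibility. The documents support neither. Each cut-off requires an observed proportion, and no section plans to claim equivalence.

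**Conclusion.** The point holds as an inconsistency between the Abstract and the Introduction, together with an adherence rule that has two readings and includes no between-format estimate. The size depends on the reading: a passing result is compatible with an observed gap of up to 20 points if 0.8 applies to each format, and with 36 points in the pooled example.

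These figures assume 55 women per format, all counted, and adherence taken as the share of women with at least six sessions. They show what the rule permits, not what the trial will find. With 55 per format the difference can be estimated to within about 15 points if both formats are near 80%, and about 12 if both are near 90%. That is enough to show a large gap but not to establish that the formats are alike. Nothing here calls for a hypothesis test or a larger sample.

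**What to change.** In the Analytic plan:

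1. State that the 0.8 adherence cut-off applies to each format separately. Keep all three cut-offs.
2. For adherence and for T2/T3 completion, report each format's proportion with a Wilson 95% CI, and the virtual minus in-person difference with a Newcombe 95% CI.
3. Count all enrolled women in the denominator, including those later excluded for non-response or low attendance.
4. Base any statement comparing the formats' feasibility on that difference. Describe it as a non-randomised comparison and give the expected half-width (about 15 points if both are near 80%, about 12 near 90%).

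If no comparison of feasibility is intended, reword the Abstract to match the Introduction's primary objective. Item 1 is needed in either case.

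The cost is a few sentences and a little extra analysis of data already being collected. Counting every enrolled woman may give a less favourable adherence figure.

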**Methods:**

In total, 165 primiparous women referring to a prenatal clinic at Milad Hospital in Tehran, will be included in this study. The subjects will be selected using the convenience sampling method and will be divided into three groups of study A, study B, and control. The study groups A and B will receive virtual and in-person childbirth training with similar content, respectively. The control group will receive only routine prenatal care. In the 18th and 20th weeks of pregnancy, the demographic information, pregnancy experience scale (PES), and version A of the Wijma delivery expectancy/experience questionnaire (WDEQ-A) will be completed, and in the 36th and 38th weeks of pregnancy, the PES and WDEQ-A questionnaires, as well as birth preference form will be completed. The type of delivery will be recorded in the first few days of postpartum.

**Conclusion:**

This quasi-experimental clinical trial will investigate the effect of virtual childbirth preparation training on primiparous women. The expected outcomes will include the difference in pregnancy experience measured by the brief version of PES, the difference in FOC measured by WDEQ-A, the birth preference, and the type of delivery.

**Trial registration:**

IRCT.ir: IRCT20180427039436N2;

**Supplementary Information:**

The online version contains supplementary material available at 10.1186/s40814-021-00933-w.

## Introduction

One of the most important goals of the World Health Organization is to achieve integrated and high-quality pregnancy care services to create positive pregnancy and childbirth experiences in women [1]. Childbirth preparation training courses prepare pregnant women for childbirth, and they are conducted individually or in a group. The ultimate goal of these courses is to improve women’s lifestyle during pregnancy and labor, and also after the childbirth while preserving the neonatal and maternal rights [2]. The advantages of prenatal pregnancy include eliminating pregnancy and delivery misconceptions, improving mother’s self-confidence regarding labor and childbirth, empowering women to select a safe delivery method, and reducing the need for analgesics during labor and childbirth [3]. On the other hand, inadequate or lack of prenatal care leads to the tendency toward cesarean section, postpartum depression, and challenges in accepting the maternal role [4].

Both pregnancy and childbirth lead to various mental and physical changes that can cause pregnant women to simultaneously experience pleasant and unpleasant feelings. On the one hand, changes, such as feeling fetal movements, thinking about the fetus, and speaking with the spouse about the newborn’s name are among the pleasant experiences during pregnancy. On the other hand, seeing common pregnancy complications in media or reading about it, and thinking about delivery and health of the neonate, especially as the due date gets closer, increases the anxiety and stress of pregnant women. Learning about changes and ways to overcome them through childbirth preparation trainings can affect the pregnant women’s pregnancy and delivery experiences and the selection of a safe delivery method [5, 6].

Studies on the effectiveness of childbirth preparation trainings have produced conflicting results [7–9]. One study showed that these trainings significantly reduce the fear of childbirth (FOC) and increase self-efficacy in pregnant women [7]. In contrast, another study found no significant effect of these trainings on reducing anxiety and increasing maternal self-efficacy [8]. Moreover, it has been reported that these trainings play a role in reducing childbirth anxiety, but have no effects on reducing the duration of labor and type of delivery [9].

Despite the efforts made to decrease the prevalence of cesarean section, this delivery method accounts for 48% of all deliveries in Iran, which is extremely above the global standard rate [10]. Given the fact that one of the important goals of childbirth preparation training courses is to reduce the rate of cesarean section, achieving this goal might and also proving the effectiveness of these trainings may require further investigations. According to previous studies, the quality of educational content and its presentation method play a significant role in the effectiveness of childbirth preparation trainings [9].

Various healthcare education methods, such as face-to-face teaching and using pamphlet, video clip, and mass media for education have been used for decades to motivate healthy behaviors in pregnant women. Nevertheless, women have increasingly become interested in using digital sources and internet to obtain information on pregnancy [11, 12]. Moreover, internet-based learning has made it possible for learners to exchange personal experiences and establish interpersonal relationship. Also, among virtual education methods, social media-based learning has been increasingly used worldwide. In Iran, the Telegram application ranks 14 among the most popular social media [11].

One of the important educational principles in healthcare is the selection of an appropriate education method to maximize the active participation of individuals [13]. Education through social media plays an important role in teaching and forming positive behaviors at the community level [14]. Some of the advantages of social media include the provision of services, such as health-related information at any time and place, online consultation, health-related question and answer, interactions between users, emotional and social support, and easy access regardless of the age, level of education, race, and place of residence [15]. Furthermore, social media are effective in shaping the attitudes of individuals by creating an interactive environment among group members [11].

Despite the rapid development of social media and their ever increasing popularity among members of the society, especially pregnant women, little research has been conducted on the virtualization of childbirth preparation training courses. In a study of teaching exclusive breastfeeding methods through Telegram social media, the mothers stated that Telegram-based education was more useful than in-person participation in the breastfeeding training courses, they also believed that Telegram social media is an effective educational tool in the field of healthcare [11]. It has also been shown that e-learning can increase the level of satisfaction and awareness of primiparous women regarding prenatal care, compared to educational booklets [16]. Although these results are promising, it is not clear whether virtualize interventions will be feasible for childbirth preparation training in Iran.

An investigation of childbirth preparation training courses showed that these courses have had little effect on pregnancy outcomes in the past few years, since the rate of cesarean sections is still high in Iran [3]. This can be attributed to factors, such as the lack of awareness and unwillingness of pregnant women to participate in natural childbirth training courses, overcrowded classes at hospitals, lack of time (especially among employed women), living far away from centers that offer such trainings, and heavy urban traffic jam, especially in densely populated cities such as Tehran.

Although attending childbirth preparation classes seems beneficial for all pregnant women, these classes are not very popular in Iran. Also, none of the studies available on e-learning in the literature has specifically targeted pregnant women, who probably would benefit the most from the lifestyle changes. Due to the importance of childbirth preparation trainings among pregnant women and ease of access to internet and virtual communication devices such as smartphone in Iran, the present study will be conducted to investigate the feasibility and the effect of childbirth preparation training courses using two in-person and virtual education methods on the pregnancy experience, FOC, birth preference, and type of delivery in pregnant women.

The primary objective of study is the feasibility of recruitment and feasibility of intervention adherence of participants in both in-person and virtual education groups. The secondary objectives are the effect of childbirth preparation training courses using two in-person and virtual education methods on the pregnancy experience, FOC, birth preference, and type of delivery in pregnant women.

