### Inclusion and exclusion criteria

All eligible pregnant primiparous women between the ages of 18 and 35 years who refer to the hospital for prenatal care at 18-20 weeks of gestation will be requested to participate in the study. Inclusion criteria are having Iranian nationality, having low-risk pregnancy^1^, having no history of infertility and mental diseases, having the ability to read and write, and having smartphone or computer with access to internet and Telegram messaging application.

After the sampling, participants who go into preterm labor, show any signs of high-risk pregnancy, wish to participate in other in-person or virtual childbirth preparation classes than the ones offered at Milad Hospital, and are unwilling to continue with the study will be excluded from the study. However, the educational content will be provided to the excluded samples that are still eager to receive them. In addition, the participants in the study group A who do not send any feedback through Telegram, and the participants in the study group B who do not attend more than two training sessions will be excluded from the study.

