### Sample size

A useful introduction to feasibility and pilot studies is given by Sim and Lewis, who recommend at least 50 participants. Therefore, according to strong evidence, sample size 50 is considered in current study [21–23].

To determine the sample size for other variables in the present study, the sample size has been calculated with a test power of 80% and a significance level of 0.05. Moreover, it is considered that in-person and social media-based education could affect the type of delivery among the study groups, leading to a 25% decrease in cesarean sections, compared to the control group. By using the effect size equation and considering 10% sample drop, the total sample size has been estimated at 55 participants per group. It should be noted that the ratio of primiparous women undergoing a cesarean section in Iran is assumed to be 0.55 [24] based on the statistics, so the sample size is large enough to measure all variables in this study.$$n=\frac{{\left({z}_{1-\alpha\left/ 2\right.}\sqrt{2\overline{p}}\overline{q}+{z}_{1-\beta}\sqrt{p_1{q}_1+{p}_2{q}_2}\right)}^2}{{\left({p}_1-{p}_2\right)}^2}=\frac{{\left[\left(1.96\times \sqrt{2\times 0.42\times 0.57}\right)+\left(0.84\times \sqrt{\left(0.55\times 0.45\right)+\left(0.3\times 0.7\right)}\right)\right]}^2}{{\left(0.55-0.3\right)}^2}=50$$$$\overline{p}=\frac{p_1+{p}_2}{2}$$

The sample size for the other variable of the study (fear of childbirth) was determined to be 43 participants with the confidence level of 95%, the power test of 80%, and based on the Toohil et al. study standard deviation for intervention and control group was 13.1 and 9.7, respectively with *d* = 7 [25], which was less than the sample size calculated based on the type of delivery. The sample size for the other two variables (childbirth experience and birth preference) was less than the one calculated for the above variables.$$n=\frac{{\left({z}_{1-\alpha\left/2\right.}+{z}_{1-\beta}\right)}^2\times \left({s}_1^2+{s}_2^2\right)}{d^2}$$$$n=\frac{{\left(1.96+0.84\right)}^2\times \left({9.7}^2+{13.1}^2\right)}{7^2}\approx 43$$

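### Type of delivery is sized on an unsourced 25-point fall in cesareans (0.55 to 0.30), and the statement that the sample is adequate for every variable is not supported

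*Protocol article*

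**What the plan says.** All references are to the protocol article.

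- **Sample size, design values.** For the outcomes other than feasibility, "the sample size has been calculated with a test power of 80% and a significance level of 0.05". Education in either format is assumed to affect type of delivery, "leading to a 25% decrease in cesarean sections, compared to the control group". The printed formula uses 0.55 and 0.30, so the 25% is an absolute fall of 25 points. No reference is attached to it.
- **Sample size, control proportion.** This does carry a reference: "the ratio of primiparous women undergoing a cesarean section in Iran is assumed to be 0.55". The same sentence goes on to conclude that the sample is adequate for all the study's variables.
- **Sample size, result.** The formula is said to give 50 per group, and "considering 10% sample drop, the total sample size has been estimated at 55 participants per group". The fear-of-childbirth calculation gives 43, so type of delivery is the outcome that sets the number.
- **Introduction, evidence on training.** Results are described as conflicting. One report found less childbirth anxiety, "but have no effects on reducing the duration of labor and type of delivery". A later paragraph says that "these courses have had little effect on pregnancy outcomes in the past few years", inferring this from the cesarean rate that remains high in Iran.
- **Inclusion and exclusion criteria.** Women aged 18 to 35 are admitted, on condition of "having low-risk pregnancy" and no history of infertility. Those who later show signs of high risk are removed.

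**The concern.** A sample size is only as good as the effect it assumes. Here the outcome that sets the number rests on a fall of 25 points from 55%, a relative reduction of 45% (0.25/0.55). No source is given, and the one direct finding the article reports for that outcome is no effect. The adequacy statement then extends this to the whole study.

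The Analytic plan tests at p < 0.05. The Discussion lists more vaginal deliveries among the main expected results and intends to carry the lessons into a large-scale grant application. If the true fall is well below 25 points, a non-significant result is likely even if training helps, and a significant one will on average be too large. A reader who accepts the adequacy statement would be misled in either case.

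**Working it through.** **Inputs.** Two-sided α = 0.05 (z = 1.96), power 80% (z = 0.84), control proportion p1 = 0.55, trained proportion p2 = 0.30, 50 per group before and 55 after allowing for 10% loss. All are from the Sample size section. Losing 10% of 55 leaves 49.5, so 50 evaluable is the planned case and 55 is the best case.

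**Step 1: the plan's own figure.** With the article's printed, rounded values:

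- 1.96 × √(2 × 0.42 × 0.57) = 1.356
- 0.84 × √(0.55 × 0.45 + 0.30 × 0.70) = 0.568
- n = (1.356 + 0.568)² / 0.25² = 59.3

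This is 60 per group. Unrounded inputs (0.425 and 0.575, exact z values) give 61. The printed 50 does not follow from the printed formula. The fear-of-childbirth figure does reproduce: 2.8² × (9.7² + 13.1²) / 7² = 42.5, or 43.

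**Step 2: power at the planned size.** The same formula solved for power is

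Φ{ [ |p1 − p2| × √n − 1.96 × √(2p̄q̄) ] / √(p1q1 + p2q2) }.

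For 0.55 against 0.30 with n = 50: (0.25 × 7.071 − 1.96 × 0.699) / 0.676 = 0.588, and Φ(0.588) = 0.72. Other values of p2, with p1 = 0.55:

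| p2 | Fall | Power, 50 per group | Power, 55 per group |
|---|---|---|---|
| 0.30 | 25 points (planned) | 72% | 76% |
| 0.35 | 20 points | 52% | 56% |
| 0.40 | 15 points | 32% | 35% |
| 0.4125 | 25% read as relative | 28% | 30% |
| 0.45 | 10 points | 17% | 18% |

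The smaller falls are assumptions chosen to show a range. The article gives no effect size from earlier work.

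The shortfall from 80% to 72% in the first row is the arithmetic slip from Step 1. The other rows are a separate matter: with 61 per group, power would still be only 60% for 0.35 and 19% for 0.45.

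**Step 3: detectable difference and precision.** With 50 per group and p1 = 0.55, power reaches 80% at a fall of 27.3 points. The 95% CI half-width is 1.96 × √[(0.55 × 0.45 + p2q2)/50], which is 0.187 for p2 = 0.30 and 0.195 for p2 = 0.45, or about 19 points.

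**Step 4: size of significant results.** Near 0.55 with 50 per group, the smallest observed difference that reaches p < 0.05 is 20 points (for example 28 against 18 women). Enumerating all pairs of binomial outcomes, significant results average 24 points when the true fall is 10, and 29 when it is 25.

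**Step 5: the control proportion.** The article gives no rate for low-risk primiparous women, so lower values are assumptions. Power with 50 per group:

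| Control | Same 25-point fall | Same 45% relative fall |
|---|---|---|
| 0.45 | 77% | 58% |
| 0.40 | 81% | 50% |
| 0.35 | 86% | 43% |

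A lower base rate raises power under one assumption and lowers it under the other.

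**The case against.** **The evidence is not all negative.** The Introduction also cites work in which training helps women choose a safe mode of delivery. The Discussion cites fear as the main reason for cesarean and a meta-analysis in which education reduces fear, and it links less fear to fewer cesareans. The statement that existing courses had little effect is a population-level inference, which the article attributes largely to poor attendance and access; this trial requires attendance at six of eight sessions. All of this stands. A reader might infer that the article's own background refutes the assumed effect. It does not: one direct null report among conflicting evidence leaves the effect open. But the favourable evidence is indirect, and none of it puts a number on the fall in cesareans.

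**Low-risk enrolment.** A reader might infer that a national rate applied to low-risk women makes the trial too small. The documents do not support that. The 0.55 is already specific to primiparous women, no low-risk rate is given, and Step 5 shows that the direction depends on which kind of reduction is held constant.

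**Overstated effects.** It is tempting to say that any significant result must exaggerate. That applies on average, and strongly only when the true fall is well below 20 points. At the planned 25 points the excess is modest.

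**Feasibility is primary.** True, and its 50 participants are justified separately. Type of delivery is listed last among the other outcomes. This limits the consequences, but the section still makes a formal efficacy calculation, lets it set the group size, and claims adequacy on that basis.

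**Conclusion.** The concern holds in a limited form. The 25-point fall has no stated source, and the adequacy statement fails for the outcome that sets the sample size. Even on the plan's own inputs, power is 72% with 50 evaluable per group and 76% with 55, against the stated 80%. It drops to 52% for a 20-point fall and 17% for a 10-point fall.

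These figures rest on a pairwise comparison of one trained group with control, a pooled-variance test at two-sided 5%, and a control proportion of 0.55. The control proportion is itself uncertain for low-risk women, but this adds doubt about an input and is not evidence of under-sizing. Nothing here affects the feasibility sample size, and the fear-of-childbirth calculation reproduces. The point is worth correcting because the article states a property that the design does not have.

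**What to change.** Keep 165 women and revise the Sample size section as follows.

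1. Describe 0.55 to 0.30 as an optimistic scenario, or cite a source for the fall if one exists.
2. Replace the stated 80% power with about 72% for 50 evaluable per group, and print the power for smaller falls: 52% at 0.35, 28% at 0.4125 and 17% at 0.45.
3. Delete the statement that the sample is large enough for all variables. State instead that a fall of about 27 points is detectable with 80% power, and that the expected 95% CI half-width is about 19 points.
4. Say that type of delivery will be reported as a difference in proportions with its 95% CI.

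Looking up cesarean rates in the hospital's own records would not settle the control proportion. Under Setting, control women are those who do not want to give birth there.

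The cost is a few reworded sentences and a less favourable power statement. No extra women are needed and no procedure changes.
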